### Assessment of safety

There were no adverse events in our initial case series evaluation of CBT-I. The following will be considered as adverse events: (i) all deaths; (ii) suicide attempts; (iii) serious violent incidents; (iv) admissions to secure units; and (v) formal complaints about therapy. We will also scrutinize any instances of patients being admitted to psychiatric hospital in the period of the therapy. These adverse events are likely to come to the attention of the assessor or therapist but we will also check medical notes at the end of each participant’s time in the trial. Responses to adverse events will be determined on a case-by-case basis by the trial team.

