## Abstract

**Background:**

Patients with psychosis frequently report difficulties getting or staying asleep (insomnia). Dissatisfaction with sleep is high. Insomnia should be treated in this group, but typically it is not even assessed. Importantly, recent evidence indicates that insomnia triggers and exacerbates delusions and hallucinations. The clinical implication is that if the insomnia is treated then the psychotic symptoms will significantly lessen. In a case series with 15 patients with persecutory delusions resistant to previous treatment this is exactly what we found: cognitive behavioural therapy for insomnia (CBT-I) led to large reductions in both the insomnia and delusions. The clear next step is a pilot randomized controlled test. The clinical aim is to test whether CBT-I can reduce both insomnia and psychotic symptoms. The trial will inform decisions for a definitive large-scale evaluation.

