**Methods/design:**

We will carry out a randomized controlled trial (the Better Sleep Trial, or the BEST study) with 60 patients with distressing delusions or hallucinations in the context of a schizophrenia spectrum diagnosis. Half of the participants will be randomized to receive CBT-I, in addition to their standard treatment, for up to eight sessions over 12 weeks. The other half will continue with treatment as usual. Blind assessments will take place at 0 weeks, 12 weeks (post-treatment) and 24 weeks (follow-up). The primary outcome hypotheses are that CBT-I added to treatment as usual will improve sleep, delusions and hallucinations compared with only treatment as usual. All main analyses will be carried out at the end of the last follow-up assessments and will be based on the intention-to-treat principle. The trial is funded by the NHS National Institute for Health Research (NIHR) Research for Patient Benefit Programme. Data collection will be complete by the end of 2014.

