## Background

Improvements in the treatment of delusions and hallucinations are greatly needed. One method for improving treatment involves drawing on developments in understanding these psychotic symptoms by targeting key putative causal factors one at a time (for example, [1-4]). Insomnia has been strongly implicated in the occurrence of psychotic symptoms but is yet to be a treatment target. Harvey et al. [5] explain: ‘Sleep disturbance is increasingly recognized as an important, but understudied, mechanism in the complex and multifactorial causation of the symptoms and functional disability associated with psychiatric disorders.’ Four recent studies by our group have established in cross-sectional and longitudinal designs that insomnia and paranoid delusions are linked [6-9]. For instance, in our initial study we found in a group of patients with persecutory delusions that 27% had severe clinical insomnia, 27% had clinical insomnia of moderate severity and 30% had subthreshold insomnia, that is, only 16% of patients were sleeping well. While it has long been known that sleep deprivation can bring on hallucinations [10] and that difficulties sleeping are one of the most common prodromal signs of psychotic disorders [11]. Moreover, Yang and Winkleman [12] have argued that their ‘data demonstrate that drug-free patients with chronic undifferentiated type schizophrenia suffer from profound disturbances in sleep continuity and sleep architecture.’ At a neurobiological level it has been suggested that the overactivity of dopamine D2 receptors in the striatum thought to underlie the positive symptoms of schizophrenia also enhances wakefulness [13]. The implication is that treating insomnia in patients with schizophrenia will lessen psychotic symptoms.

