### Planned interventions

The insomnia intervention will be provided in up to eight sessions over 12 weeks. The 12-week window will allow some flexibility for appointment times (it is quite common for patients in this group to fail to attend appointments) and the extension of intervals between the final two sessions. The exact number of sessions will depend on clinical appropriateness in the 12 week window. The main techniques, which are standard sleep interventions for CBT, are taken from four main sources [15,21-23]. The intervention is written in a manual, which we will develop further. Initially, the sessions focus upon psycho-education about sleep difficulties, assessment of the triggering and maintenance of sleep difficulties, and goal-setting. There is a checklist of factors likely to cause sleep difficulties. Based on the assessment, the active therapeutic techniques that are used included sleep hygiene, stimulus control therapy (for example, setting appropriate and regular sleep times, not doing anything else in the bed or bedroom apart from sleeping, not staying in bed if not able to sleep for longer than 20 to 30 minutes, stopping daytime naps), relaxation, and, less often, cognitive techniques to address unhelpful beliefs and attitudes about sleep, attentional bias, monitoring, and safety behaviours. The intervention is deliberately simplified, with the principal therapeutic technique being stimulus control; that is, learning to associate bed with sleep. Participants are also given written information as part of the intervention in the form of leaflets to read between sessions and on completion of the intervention. The intervention will be carried out by a qualified clinical psychologist, who carried out the case series therapy. Sessions will be taped for assessment of adherence and for competence [24]; when the purpose is clearly explained, we have found that 80% of patients with psychosis agree to recordings of sessions. We will obtain independent judgements on the quality of therapy using a random selection of therapy tapes. Patients will also be asked to assess the therapist’s empathy [25]. Standard care is delivered according to national and local service protocols and guidelines. Service use will be measured using the Client Service Receipt Inventory [26].

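### The adverse-event list omits worsening of psychosis or sleep and includes an item that in practice only CBT-I patients can trigger; individual deterioration, which a mean difference can hide, is not planned as a harm outcome

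*Protocol article*

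**What the plan says.** Assessment of safety in the protocol article defines the events: "The following will be considered as adverse events: (i) all deaths; (ii) suicide attempts; (iii) serious violent incidents; (iv) admissions to secure units". The fifth and last item is "v) formal complaints about therapy". The section then adds: "We will also scrutinize any instances of patients being admitted to psychiatric hospital in the period of the therapy". Events are expected to reach the assessor or the therapist, and "we will also check medical notes at the end of each participant’s time in the trial".

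The control arm receives no trial therapy: "The other half will continue with treatment as usual" (Abstract, Methods/design).

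Two statements link poor sleep to psychosis. The Abstract says that "recent evidence indicates that insomnia triggers and exacerbates delusions and hallucinations". The Background says that "it has long been known that sleep deprivation can bring on hallucinations". Planned interventions names stimulus control as the principal technique and gives as examples "not staying in bed if not able to sleep for longer than 20 to 30 minutes, stopping daytime naps".

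Outcome measures makes the ISI and the PSYRATS the key outcomes and also records adverse events and hospital admission data. Assessment and follow-up sets blind assessments at 0, 12 and 24 weeks. Statistical analysis plans analysis of covariance for continuous outcomes, and absolute risk difference and relative risk for binary outcomes, without naming the binary outcomes.

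**The concern.** The article describes the trial as the first controlled test of CBT-I in this population. The earlier evidence it gives is an uncontrolled series of 15 patients with no adverse events. What this pilot says about harm will therefore inform the decision on a Phase III trial.

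In a trial that recruits people with distressing delusions or hallucinations and treats their sleep, worsening of those problems is an obvious harm to look for. It is not on the list. A report of no adverse events under this definition would not address it.

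The complaints item raises a separate problem. It sits in the same definition as deaths and suicide attempts, but a control patient has no trial therapy to complain about. Any comparison of adverse events between arms that included it would not be like for like.

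**Working it through.** The article gives no safety rate, deterioration margin or safety power, so there is no stated figure to reproduce. The sample size of 60 rests on recruitment experience. Taking 30 per arm (60, half to each), the check has four parts. All rates and effect sizes below are assumptions.

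**1. Coverage, by reading**

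| Possible harm | Where it would appear | Gap |
|---|---|---|
| Average worsening of sleep or psychosis | Analysis of covariance on ISI and PSYRATS | None at 12 and 24 weeks |
| Worsening that leads to psychiatric admission | Scrutiny of admissions; admission data; notes check | Scrutiny limited to the therapy period, which has no counterpart for controls and excludes weeks 12 to 24 |
| Worsening in individuals without admission | No harm outcome stated | Not covered |
| Complaint about therapy | Fifth listed event | In practice one arm only |

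Detection is also somewhat uneven: a therapist is one route by which events come to light, and only the CBT-I arm has a trial therapist. The notes check at the end of each participant's time in the trial partly offsets this.

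**2. What a mean can hide**

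If a fraction f of an arm worsens by w SD and the rest improve by g SD, mean improvement = (1 − f) × g − f × w.

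- f = 0.10, w = 1.0, g = 0.5: 0.9 × 0.5 − 0.1 × 1.0 = 0.35 SD.
- f = 0.20, w = 0.5, g = 0.8: 0.8 × 0.8 − 0.2 × 0.5 = 0.54 SD.

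In the first case the worsening patients lower the mean by 0.5 − 0.35 = 0.15 SD. The 95% half-width for a difference in means at 30 per arm, without covariate adjustment, is 1.96 × √(2/30) = 0.51 SD. A shift of 0.15 SD could not be distinguished from noise.

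**3. What the listed events can show**

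- P(at least one event in 30) = 1 − (1 − p)^30: 26% at p = 1%, 45% at 2% and 79% at 5%.
- With zero events in 30, the one-sided 95% upper limit is 1 − 0.05^(1/30) = 9.5%, and the two-sided exact upper limit is 1 − 0.025^(1/30) = 11.6%.

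These limits follow from the size of the trial, not from the choice of list. They show that a clean record would be weak reassurance even for the events that are listed.

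**4. What a deterioration count would show**

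- Exact 95% interval for 3 of 30: 2% to 26%. For 6 of 30: 8% to 39%.
- Risk difference for 6 of 30 v 3 of 30: 0.20 − 0.10 = 0.10, with standard error √(0.2 × 0.8/30 + 0.1 × 0.9/30) = 0.091. The approximate 95% interval is −8 to +28 percentage points.
- Power at two-sided 5%: 19% for 10% v 20%, 49% for 10% v 30% and 78% for 10% v 40%.

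The count would be descriptive. A composite over three scales and two visits would add noise: with an assumed 5% chance crossing per comparison, independent, 1 − 0.95^6 = 26% of patients would be flagged. Each scale should therefore be reported separately.

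**The case against.** The case against has real force. The ISI and the PSYRATS are the key outcomes, rated blind in both arms and supported by a psychiatric interview scale, a second sleep index, a paranoia scale, sleep diaries and actigraphy. A reader might infer from the adverse-event list that worsening of psychosis or sleep would go unreported. The article does not support that: an average worsening would appear in the main analysis.

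The list is also not the whole of the safety section. Psychiatric admissions are scrutinised, admission data are recorded and every participant's notes are checked. That stands, but the scrutiny is tied to the therapy period, and admission misses deterioration managed without it.

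No pooled adverse-event total or between-arm test is planned. A reader might infer a count tilted against CBT-I, but the article sets out no such count. What stands is narrower: the complaints item cannot be compared between arms if a comparison is made.

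A reader might also infer that the protocol's own model predicts harm from CBT-I. It does not. It says lost sleep can worsen psychosis, but never that CBT-I reduces sleep; it predicts improvement, and 14 of the 15 patients in the case series cut their insomnia scores by at least 25%. That leaving bed and stopping naps could cost some patients sleep is an inference: reason enough to look, but not evidence of harm.

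Finally, a detailed statistical analysis plan is promised and may contain a deterioration table. Its absence here would be no finding on its own. The adverse-event definition, however, is stated in the article and can be judged as written.

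**Conclusion.** The concern holds in a limited form. The stated definition of adverse events captures the most relevant harm poorly and includes one item confined in practice to the CBT-I arm. The admission scrutiny narrows the gap but does not cover both arms over the same 24 weeks. Average worsening is covered by the main analysis; individual deterioration is not stated as a harm outcome and can be hidden by the mean, as the 0.35 SD example shows.

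The size of the problem cannot be estimated from the article, because it gives no deterioration rate. The examples show only that masking is possible at plausible values. Nothing stated is false or contradictory, and the efficacy analysis is unaffected. This is a low-cost improvement to harm reporting.

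**What to change.** 1. Before analysis, set a deterioration margin for each scale. Report by arm the number of patients worse than baseline by that margin on PSYRATS delusions, PSYRATS hallucinations and ISI, each scale separately, at 12 and 24 weeks. Give the risk difference, already planned for binary outcomes, with a confidence interval, and label the table descriptive.
2. Report psychiatric admissions in both arms over the same 0 to 24 weeks, from the admission data and notes check already planned.
3. Report formal complaints about therapy separately, outside any between-arm comparison of adverse events.

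The cost is a short safety table, a few agreed margins and a wording change, with no new visits or measures. There are three drawbacks. Some flagged worsening will be score fluctuation, although the control arm shows how much to expect. Estimates will be imprecise at 30 per arm. Patients near the top of the ISI have little room to worsen: entry requires at least 15, and the high-severity stratum runs from 22 to 28.

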### Statistical analysis

All main analyses will be carried out at the end of the last follow-up assessments (that is, there will be no interim analyses) and will be based on the intention-to-treat principle, with due consideration given to potential biases arising from loss to follow-up. Parameter estimates and confidence intervals of continuous outcomes will be obtained using analysis of covariance, adjusting for baseline variables. (We will also look at the effect of treatment difference by controlling for initial overall symptom severity (assessed by the Positive and Negative Symptom Scale) and medication use as a sensitivity analysis). Absolute risk difference and relative risk will be calculated for binary outcomes. Rates of attrition and loss to follow-up will be calculated for each time point. We will also assess the correlations of each measure across all time points. These findings will be used to inform the sample size for the definitive trial. For the health economic analysis, quality adjusted life-years will be used as an outcome measure, by combining EQ-5D quality-of-life information with survival data. A cost-utility analysis will be performed, in which the differences in mean costs between the CBT and standard care groups will be divided by the difference in mean outcomes between the two groups. The sample size of 60 is based on our collective recruitment experience from previous and current studies, and is considered adequate for obtaining reasonably reliable sample size estimates [40]. The patients will be recruited over 15 months. A fully detailed statistical analysis plan will be written and signed off by the investigator prior to any analysis by the trial statistician.

## Discussion

The importance of sleep in the occurrence of psychiatric problems is becoming increasingly recognized [5,41]. The BEST study will be the first randomized controlled test of cognitive behaviour therapy for insomnia in patients with nonaffective psychosis. The trial is funded for 24 months and staff began in post in October 2012. Final outcome assessments will be complete by the end of August 2014. Therefore, the study results will become available in 2015. We predict that the intervention will not only improve sleep but lessen distressing positive symptoms of psychosis. Our experience is that the intervention is popular since it focuses on a problem that the patient recognizes and hence there is a clear shared outcome goal. In the study we will be able to compare self-reported and more objective markers of sleep (for example, actigraphy, melatonin), while we will assess delusions and hallucinations multidimensionally (for example, frequency, preoccupation, distress, and interference). If the study is successful, we anticipate that the next step will be a definitive Phase III clinical trial. We think it likely that in the future the treatment of sleep problems will be an important tool in the reduction, and perhaps prevention, of distressing psychotic experiences.

### Trial status

Patients began to enter the trial in December 2012. Recruitment will continue for 15 months.

## Abbreviations

CBT-I: Cognitive behavioural therapy for insomnia; ISI: Insomnia Severity Index; NIHR: National Institute for Health Research; PSYRATS: Psychotic Symptom Rating Scales.
